### Participant timeline

Treatment is provided according to the following timeline (Table 2):T = day 0 → outpatient clinic treatment with either SCL or RBL after providing written informed consent to the treating physician.T = day 7 → telephone appointment with a blinded researcher: the PROM and PREM questionnaires are completed by the researcher.T = 6 → weeks outpatient clinic appointment with a physician. The PROM and Wexner incontinence scale are completed together with a physical examination. If needed, the same treatment (SCL or RBL) is repeated.T = 6 → months telephone appointment with a blinded researcher: PROM questionnaire completed and (subjective) symptoms related to recurrence are assessed.

**Table 2 Tab2:** Participant timeline

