#### Secondary outcomes

Secondary outcome measures consist of patient experience outcomes (PREMs), number of treatments, crossover and number of days on work leave.

Patient experience outcomes are recorded on the PREM questionnaire (Appendix). It contains a series of questions regarding the patients’ experience of the treatment, which is partly scored on a Likert scale ranging from 1 (“not at all”) till 5 (“very much”). Two additional binary (yes/no) questions are added regarding whether patients would undergo the same treatment and whether they would recommend the treatment to acquaintances suffering from similar HD symptoms. The administration of this questionnaire takes place 1 week after treatment. The total number of treatments, the crossover of treatment arms and days of work leave are recorded after a total of 6 months of follow-up. All data entries are stored in Castor^EDC^.

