**Secondary outcomes**				
Satisfaction/experience (PREM)		X		
Absenteeism		X	(X)	
Number of treatments			X	X
Crossover rate				X

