### Recruitment and blinding

In the Netherlands patients with HD are mostly referred to the surgeon by their general practitioner. The outpatient clinic nurses or researchers will screen for eligibility and send the patient written information (study information folder (PIF) and plan their appointment at the outpatient clinic. This allows for a minimum of 48 h to reflect on the information. The patient takes the information to the outpatient clinic appointment to discuss with the treating physician. In the case of participation, oral and written consent are gathered.The treating physician generates the allocation process or registration to the preference arm, after written informed consent has been provided.The randomization sequence will be computer generated with the Castor^EDC^ program (version 24.41) without stratification, with 1:1 allocation to either group, generating a unique record number.Both patient and treating physician are not blinded for the treatment arm.In concept, the researcher who completes the telephone interviews at 7 days and 6 months is blinded to the given therapy and is instructed not to actively ask patients which treatment they received. However, the data is added in the same database system, so complete blinding is not guaranteed. The physician at T = 0 and T = 6 weeks is not blinded as it is otherwise impossible to complete the treatment. Also, at 6 weeks the treating physician should repeat the initial treatment when necessary, following protocol.

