### Data collection

Each participating centre’s personnel involved in treating patients with HD are trained in providing eligible patients with both oral and written information about the study. All the medical baseline and procedure data are collected at the individual hospitals. The data is stored in standardized case record forms (CRFs) within Castor.

The surgeons involved in treating patients with HD are responsible in collecting the data from the initial visit/treatment and the 6-week outpatient visit where complications are scored. Research personnel of each participating centre is responsible for their own data collection during the 6-month follow-up period.

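### The 6-week PROM is taken within a visit to an unblinded physician who may retreat, and the 6-month caller is not securely blinded; both gaps in assessor blinding are cheap to narrow

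*Protocol article*

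**What the plan says.** All references are to the Protocol article.

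- **Outcome.** Primary outcomes and Table 1 make the five-symptom PROM (range 5 to 25) a primary outcome, collected at baseline, 1 week, 6 weeks and 6 months. Treatment efficacy classes any fall in score as improvement and turns this into yes or no.
- **1 week.** Participant timeline assigns the PROM to a blinded researcher by telephone.
- **6 weeks.** The same section describes an outpatient appointment with a physician: "The PROM and Wexner incontinence scale are completed together with a physical examination". The same treatment is repeated if needed. Recruitment and blinding states: "The physician at T = 0 and T = 6 weeks is not blinded as it is otherwise impossible to complete the treatment". Data collection says that the surgeons "are responsible in collecting the data from the initial visit/treatment and the 6-week outpatient visit where complications are scored".
- **6 months.** Participant timeline gives: "months telephone appointment with a blinded researcher: PROM questionnaire completed and (subjective) symptoms related to recurrence are assessed". Secondary outcomes says that "The total number of treatments, the crossover of treatment arms" and days of work leave are recorded after 6 months of follow-up, and names no recorder. Table 2 marks number of treatments and "Crossover rate" in the column headed as the 6-month telephone contact, which also holds the PROM and recurrence.
- **Limit on blinding.** Recruitment and blinding says that the telephone researcher is blinded in concept and told not to ask actively about treatment. It then adds: "However, the data is added in the same database system, so complete blinding is not guaranteed". It also states that patients are not blinded.

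**The concern.** The protocol uses a blinded telephone interviewer at two of the three follow-up points, so it regards assessor blinding as worth having for this outcome. At the third, the PROM sits inside a consultation with an unblinded physician who may decide on retreatment at the same visit. A physician's view of one technique, or the pending retreatment decision, could influence the answers. Because success is any fall in score, one point can change a patient's result.

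At 6 months, a caller who can see the allocation in the database, or who discusses the direction of a crossover with the patient, may learn the arm before the PROM and recurrence are recorded.

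The trial tests non-inferiority against a 10-point limit. A bias that differs between arms could therefore move the conclusion either way: towards accepting an inferior treatment, or towards missing a comparable one.

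**Working it through.** **1. Who takes the PROM, and with what knowledge of the arm**

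| Time | Setting | Assessor as described | Blinded? |
|---|---|---|---|
| 1 week | telephone | researcher | in concept; shared database |
| 6 weeks | outpatient visit, with physical examination and possible retreatment | not named; physician present, surgeons responsible for the visit's data | physician is not |
| 6 months | telephone | researcher | in concept; shared database |

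The reason given for the unblinded physician is that treatment could not otherwise be given. That covers the treatment and arguably the physical examination. It does not cover a symptom questionnaire that the patient could complete beforehand.

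**2. What the 6-month contact contains**

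Participant timeline lists only the PROM and recurrence symptoms. Table 2 also marks number of treatments and crossover under that contact. The text and the table therefore differ on whether the call includes these two items, and no section says who records them.

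**3. The plan's own sample size**

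Inputs from Sample size calculation: 70% success in both arms, 10-point limit, 80% power, alpha 2.5%.

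n per arm = 2 × 0.70 × 0.30 × (1.960 + 0.842)² / 0.10² = 329.7, rounded up to 330. This matches the stated 330 per arm (660 in total). It is obtained with 2.5% one-sided, although the section calls the level two-sided, so one-sided 2.5% is used below.

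**4. Illustration: what a differential bias would do**

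The document gives no size or direction for such a bias; 4 points is assumed.

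*Bias towards SCL when SCL is truly 10 points worse (60% vs 70%):*
- SE = √[(0.70 × 0.30 + 0.60 × 0.40) / 330] = 0.0369
- P(declare non-inferior) = Φ(0.04 / 0.0369 − 1.96) = Φ(−0.88) ≈ 0.19, against 0.025 with no bias

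*Bias against SCL when the arms are truly equal (70%):*
- SE = √(2 × 0.70 × 0.30 / 330) = 0.0357
- Power = Φ((0.10 − 0.04) / 0.0357 − 1.96) = Φ(−0.28) ≈ 0.39, against 0.80 with no bias
- With the SCL variance taken at the biased rate of 66%, SE = 0.0363 and power ≈ 0.38

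*Range over the assumed bias (same formulas, first variance):*

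| Assumed bias | False non-inferiority | Power |
|---|---|---|
| 0 points | 2.5% | 80% |
| 2 points | 7.8% | 61% |
| 3 points | 12.6% | 50% |
| 4 points | 19% | 39% |
| 5 points | 27% | 29% |

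**5. From score to success rate**

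Assume a roughly normal change score with an SD of 3 to 5 (not given in the protocol) and 70% success, so that Φ⁻¹(0.70) = 0.524. A shift of 0.5 point in one arm only changes success by Φ(0.524 ± 0.5/SD) − 0.70. This is +3.4 to +5.5 points, or −3.6 to −6.0 points, for SD 5 to 3. A small arm-specific shift in score would therefore be enough, if it occurred, to produce a bias of the order used above.

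**The case against.** The strongest reply is that this is an open-label trial with a patient-reported outcome and that its limits are disclosed. The protocol says that the 6-week physician is unblinded and that the caller's blinding is incomplete. The patient, who supplies every PROM answer, knows the treatment at all time points, and no change of interviewer alters that. Some of the suspected effects, such as under-reporting to one's own doctor or the change of assessor and mode between visits, occur in both arms and need not bias the comparison. Detailed database permissions may also be set out in the full protocol. All of this stands, and it limits the weight of the point.

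Several stronger readings are tempting but are not supported:

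- *The physician scores the 6-week PROM.* The sentence is passive and names nobody, whereas the day-7 entry names the researcher. Surgeons' responsibility for the visit's data is compatible with a form filled in by the patient.
- *The blinded caller must record crossover and treatment counts.* Only the Table 2 column suggests it. The description of the call omits both, and they could come from the clinic record.
- *Recording these items reveals the arm.* A count does not, and neither does a yes or no on crossover; the direction of a crossover would. Crossover is permitted only after at least two treatments, so it concerns a subset of patients.
- *Planned blinding is lost at 6 weeks.* None was planned there.

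What remains is that the setting of the 6-week PROM is avoidable, its assessor is unstated, and the routes by which the caller could be unblinded can be narrowed. Disclosing a weakness does not reduce it.

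**Conclusion.** The point holds as a low-cost improvement, not as a hidden contradiction or a fatal flaw. A primary outcome is collected at 6 weeks within a visit to an unblinded physician who may retreat, and the reason given for not blinding does not require that arrangement. At 6 months the caller's blinding is insecure, as the protocol concedes, and Table 2 adds a further possible route to unblinding.

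The size of any resulting bias cannot be derived from the document. A reader might take the 19% and 38–39% as estimates of the trial's error rate and power. They are not: they show what an assumed 4-point differential bias from any cause would do with 330 per arm at one-sided 2.5%. They also treat a single time point as decisive, which the article does not specify. The proposed changes would reduce the assessor's contribution only; expectation bias from unblinded patients would remain.

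**What to change.** 1. **6 weeks.** State in Participant timeline that the patient completes the PROM and the Wexner score alone, on paper or as a Castor survey, before the consultation and before any decision on retreatment.
2. **Treatment counts and crossover.** Take both from the procedure CRFs held at the hospitals. Amend Table 2 so that they no longer appear as part of the blinded telephone contact, in line with Participant timeline.
3. **Telephone calls.** Give the caller a database role that hides the allocation and procedure forms, and take the PROM and recurrence first in the call.

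Cost: a short amendment plus survey and user-role settings, with no extra staff or visits. The downsides are some incomplete self-completed forms and a self-completed mode at one time point only, which should be borne in mind when scores are compared across visits. No treatment rule changes.

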## Introduction

### Background and rationale

Haemorrhoids are a part of normal anatomy, and yet the term haemorrhoids is often used to refer to haemorrhoidal disease (HD) in which clusters of vascular tissue, smooth muscle and connective tissue in the anal canal give rise to symptoms of blood loss, itchiness, soiling and/or prolapse [1]. HD is a common condition with significant epidemiologic and economic relevance. The prevalence of HD rises up to 55% for adults aged between 45 and 65 years of age, with an annual incidence of 5% of the general population [2].

In 1985, Goligher was the first to report a widely accepted grading system for haemorrhoids, which describes four separate groups based on the extent of prolapse inside, or outside, the anal canal [3]. In 460 B.C., Hippocrates described HD with a plethora of treatments, varying from burning, herbs, ligation and surgical excision [4]. Currently, various treatments are available to treat HD [5, 6].

Symptomatic grade 1–2 haemorrhoids can be treated with either rubber band ligation (RBL) or sclerotherapy (SCL) and both treatment options often require multiple sessions [6]. The most common symptom for this patient population is rectal blood loss accompanying defecation [3, 7]. RBL is based on the strangulation and necrosis of haemorrhoidal tissue, resulting in fibrosis and fixation to the surrounding anal mucosa [5, 8]. The most important disadvantages are the feeling of urgency, pain and soiling during and after the procedure. A rare but serious complication of RBL is the occurrence of an arterial bleeding, which in some cases needs to be stopped surgically. On the contrary, SCL induces an inflammation process and local sclerosis of the submucosa which initiates fixation of the haemorrhoidal tissue to the anorectal wall [6, 8]. The haemorrhoid shrinks through the obliteration of the vascular wall. Current literature does not describe major negative side effects, with only a few cases of local infection and haemorrhoidal thrombosis, and very rare complications such as fistula formation and impotence [6, 8]. In the event of haemorrhoidal thrombosis, oral pain medication is usually sufficient; surgical incision of the clot is scarcely required. Another agent that is used in the treatment of HD is phenol. A study showed that it can be equally effective as Aethoxysklerol; however, the use of phenol led to more adverse reactions such as pain, necrosis and ulceration [9].

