Furthermore, a recent study has shown a lack of uniformity in the definitions for outcomes, when considering a successful treatment of HD [10]. This results in heterogeneity, limited transparency and hampers the ability to adequately compare results. The most common outcomes in HD studies are pain, blood loss, prolapse and incontinence. Results from a systematic review found no significant difference in the effectiveness of RBL and SCL in treating HD in terms of blood loss, recurrences and complications (73–84% vs 69–88%, 10–18% vs 1.5–29%, and 8–80% vs 34–49%, respectively) [6, 8]. In the present time, similar effectiveness in terms of subjective outcomes (PROMs) and patient experience outcomes, such as satisfaction rates and the subjective experience of a treatment, are important and distinctive measures. These experience measures are scarcely reported in current literature.

In May 2019, the first Core Outcome Set (COS) for HD was developed by the European Society of Coloproctology (ESCP) [11]. The primary outcomes are objective symptoms, complications and recurrences. The patient experience from each treatment will be monitored as a secondary outcome. Symptoms should be scored according to standardized PROMs (blood loss, itchiness, soiling, pain and prolapse). Complications such as incontinence, abscess, anal stenosis and fistula formation need to be reported, together with the recurrence of symptoms (subjective recurrence of disease).

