### Outcomes

#### Primary outcomes

The primary outcome measures are treatment efficacy measured through PROMs according to the ESCP core outcome set of symptom reduction, subjective recurrences and complications (Table 1). The follow-up period for this outcome set is 6 months, and data will be collected at 4 different time points during this period (baseline, 1 week, 6 weeks and 6 months after the first procedure).

**Table 1 Tab1:** Primary and secondary outcome measures

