	**Tools of measurement**
**Primary outcomes**	
*Patient-related outcomes*	PROM (minimal score 5, maximum score 25): The lower the score the better the result
- Blood loss	Likert scale – 1 (not at all) to 5 (very much)
- Pain	Likert scale – 1 (not at all) to 5 (very much)
- Prolapse	Likert scale – 1 (not at all) to 5 (very much)
- Itching	Likert scale – 1 (not at all) to 5 (very much)
- Soiling	Likert scale – 1 (not at all) to 5 (very much)
	HISS (minimal score 0, maximum score 20)
- Impact on daily activities	Scale – 0 (no impact at all) to 10 (highly impacted on daily activities)
- Satisfaction with treatment	Scale – 0 (not at all satisfied) to 10 (very satisfied)
*Complications*	
Incontinence	Wexner Fecal Incontinence Score
Abscess	Physical examination^a^
Fistulation	Physical examination^a^
Urine retention	Bladder scan
Anal stenosis	Physical examination^a^
Anal fissure	Physical examination
Arterial bleeding	Physical examination
Thrombosed haemorrhoid	Physical examination
*Recurrence*	Subjective return of initial symptoms

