#### Treatment efficacy

This outcome follows the patient-reported outcome measure-haemorrhoidal impact and satisfaction score (PROM-HISS) questionnaire from the international Delphi procedure of the European Coloproctology group, for which recently the first steps in the validation process were taken [10, 11, 13].

This questionnaire consists of three domains: (1) HD symptoms, (2) impact of HD on daily activities, and (3) satisfaction with treatment [13]. The first domain contains five HD symptoms of which each is scored on a Likert scale ranging from 1 (“not at all”) till 5 (“very much”), resulting in a maximum possible score of 25. During follow-up, any reduction in score on this numeric scale is classified as ‘improvement’. This will then be translated into a binary outcome: “yes” or “no” improvement of symptoms. Both the second and third domains only contain one item, the impact of HD on daily activities and patients’ satisfaction with treatment, respectively. Both are scored on a 10-point numeric rating scale. In respect to the impact of symptoms on daily activities, 0 correlates with “no impact at all” and 10 with “highly impacted on daily activities”. On the contrary, for patient satisfaction with treatment, this ranges between 0 “not at all satisfied” and 10 “very satisfied”. Data from the PROM-HISS questionnaire is collected 1 week after the procedure, so the recall period comprises “the past week” [13].

Complications (i.e. incontinence, abscess, fistula, fissure, urine retention, anal stenosis, arterial bleeding or thrombosed haemorrhoid) are scored at the 6–8 week clinical follow-up appointment at the outpatient clinic. Subjective return of initial symptoms (recurrence) is recorded during the 6-month follow-up period.

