**Primary outcomes**				
HD symptoms (PROM)	X	X	X	X
Abscess			X	
Urine retention			X	
Anal stenosis			X	
Incontinence			X	
Fistula			X	
Recurrence			X	X

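### The Wexner incontinence score, part of the primary complication outcome, is taken only at 6 weeks, so it cannot by itself separate new or worsened incontinence from incontinence present before treatment.

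*Protocol article*

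**What the plan says.** Table 1 of the protocol article places complications under the primary outcomes. Incontinence is the first complication listed, and its instrument is the "Wexner Fecal Incontinence Score". No threshold and no change-from-baseline rule is given.

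Three places fix the timing, and they agree:

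- Participant timeline, 6-week visit: "The PROM and Wexner incontinence scale are completed together with a physical examination". The Wexner scale is not named at day 0, day 7 or 6 months.
- Table 2: the incontinence row has one mark, in the 6-week column. The PROM row of the same table is marked at baseline and at all three later time points.
- Treatment efficacy: complications "are scored at the 6–8 week clinical follow-up appointment at the outpatient clinic".

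The Background says that haemorrhoids can "give rise to symptoms of blood loss, itchiness, soiling and/or prolapse". The Eligibility criteria exclude grade 3 and 4 haemorrhoids and treatment for the disease in the previous 12 months. They do not exclude prior incontinence.

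**The concern.** An abscess or an arterial bleed after treatment is an event and can be counted without a baseline. A Wexner score is a level, and it shows harm only against an earlier level in the same patient. Some patients may already leak at entry, so part of what the 6-week score records may belong to the disease and not to the treatment.

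Two results depend on this. The trial hypothesises that sclerotherapy is not inferior on complications, and the Statistical analysis section tests primary outcomes with chi-square or Fisher's exact test. Pre-existing cases in such a test add noise and pull relative differences toward equality. The interim analysis, after 300 randomised patients have completed 6 months, also compares the numbers of patients with complications. A patient who leaked before treatment could already be in that count.

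The gap is in data collection. If no baseline score exists, no later analysis plan can define a change from it.

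**Working it through.** **The plan's own figure.** The article gives no expected rate for incontinence. Its only sample-size figure concerns symptom reduction: n = (1.960 + 0.842)² × 2 × 0.70 × 0.30 / 0.10² = 329.7, or 330 per arm at one-sided 2.5%. This reproduces the stated number and does not depend on the present point.

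**Illustration 1: share of pre-existing cases and precision.** Assumptions, none of them in the documents: new onset in 3% of patients; prior leakage in a proportion b, equal in both arms; prior leakage still present at 6 weeks; any positive score recorded as a case.

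- Recorded rate = b + 0.03
- Pre-existing share = b / (b + 0.03)
- Standard-error ratio = √[(b + 0.03)(1 − b − 0.03) / (0.03 × 0.97)]

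| b | Recorded rate | Pre-existing share | Standard-error ratio |
|---|---|---|---|
| 2% | 5% | 2/5 = 40% | √(0.0475/0.0291) = 1.28 |
| 5% | 8% | 5/8 = 63% | √(0.0736/0.0291) = 1.59 |
| 10% | 13% | 10/13 = 77% | √(0.1131/0.0291) = 1.97 |
| 20% | 23% | 20/23 = 87% | √(0.1771/0.0291) = 2.47 |

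**Illustration 2: a true difference between arms.** Assumed new onset among initially continent patients is 2% against 6%, with 330 per arm and a two-sided 5% test. The 6-week rate in each arm is b + (1 − b)p. Power is the normal approximation Φ{[|p₂ − p₁| − 1.96√(2p̄(1 − p̄)/n)] / √([p₁(1 − p₁) + p₂(1 − p₂)]/n)}. The new-onset column uses n = 330(1 − b).

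| b | 6-week rates | Difference (points) | Risk ratio | Power, 6-week rate | Power, new onset only |
|---|---|---|---|---|---|
| 0 | 2.0% vs 6.0% | 4.0 | 3.0 | 75% | 75% |
| 5% | 6.9% vs 10.7% | 3.8 | 1.55 | 41% | 73% |
| 10% | 11.8% vs 15.4% | 3.6 | 1.31 | 27% | 70% |
| 20% | 21.6% vs 24.8% | 3.2 | 1.15 | 16% | 65% |

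The absolute difference shrinks only by the factor (1 − b). The loss comes mainly from added variance and, on the ratio scale, from the larger denominator. These power figures concern incontinence alone, not all complications combined.

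**The case against.** A reader might infer four stronger things from the schedule, and the article supports none of them.

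1. **That every positive 6-week score counts as a complication.** No such rule is stated. Table 1 names only an instrument, and a case definition may stand in a fuller document. The treating physicians, who see patients at day 0 and at 6 weeks, could also judge onset by history. That judgement would be retrospective and made by someone who is not blinded, so it does not replace a baseline score.

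2. **That prior leakage is unknowable.** The PROM is taken at baseline and includes a soiling item scored 1 to 5, so patients who soiled at entry can be identified. The Background treats soiling as a symptom and incontinence as a complication, and one soiling item cannot be subtracted from a Wexner score. By the same separation, the article does not say that patients who soil score positive on the Wexner scale.

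3. **That the comparison is biased.** Allocation is 1:1 at random, so prior incontinence balances on average. The comparison of 6-week scores is valid as such, but it is a diluted measure of new incontinence. The preference arms are not randomised and lack this balance.

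4. **That the interim rule is wrong.** It compares arms, and significant differences lead to a discussion by the study group. A rate raised equally in both arms makes that look less sensitive and does nothing more. Incontinence is also one of eight complications named under Treatment efficacy.

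It is also fair to say that the sample size rests on symptom reduction, so the trial's main calculation is untouched.

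**Conclusion.** The point holds in this limited form. The printed schedule measures a primary-outcome complication once, after treatment, in patients who may have had incontinence before it. The 6-week score alone cannot separate new or worsened incontinence from what was already there. The incontinence rate may be overstated in both arms, and a true difference may be diluted toward no difference, in the final analysis and at the interim look.

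The size is unknown because the article gives no prevalence. With 3% new onset and 2% to 20% prior leakage, 40% to 87% of recorded cases would be pre-existing and the standard error about 1.3 to 2.5 times larger. These figures assume that prior leakage persists to 6 weeks and that any positive score is recorded as a case. If leakage resolves with treatment, or a stricter case definition applies, the effect is smaller.

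**What to change.** - Add the Wexner scale to the baseline column of Table 2. Table 2 allows baseline data at allocation or by telephone, so state that the scale is completed before treatment and, where possible, before allocation.
- Define the complication as new or worsened incontinence relative to baseline, and adjust the 6-week score for the baseline score.
- For patients already enrolled without a baseline Wexner score, report the 6-week score by arm as randomised, with the baseline PROM soiling item as a covariate.
- In the preference arms, where allocation gives no balance, show incontinence alongside the baseline score.

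The cost is one short questionnaire at a contact that already exists, and incomplete baseline data for patients enrolled earlier. The 330 per arm does not change. Each further patient treated without the score is one for whom it cannot be recovered.
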